#### 2.4.1 Primary outcome—cognition

Cognitive functioning is assessed using a battery of validated paper-pencil and interview-based neuropsychological assessments and computerized cognitive tasks. All assessments are performed under the supervision of a neuropsychologist or a trained psychology student. The neuropsychological tests are administered in a fixed order: MoCA (Nasreddine et al., 2005), Rey auditory verbal learning test—RAVLT (Lezak et al., 2012), Digit Symbol Substitution Test—DSST (Jaeger, 2018), Stroop Color-Word Interference Test—SCWIT (Jensen and Rohwer, 1999), Phonological and Semantic Fluency from the D-KEFS battery (Letters P, T, L – 60 s maximum) (Delis et al., 2001), Trail Making Test—TMT A and B (Tombaugh, 2004), Digit Span and Similarities subtest from the WAIS-IV (Wechsler, 2008). All the above tests are validated and normalized for an older adult population (Lezak et al., 2012; Strauss et al., 2006).

First, the Montreal Cognitive Assessment (MoCA) score will measure global cognition (Nasreddine et al., 2005). Then, the executive functions, processing speed, and episodic memory will be assessed by three composite Z-scores calculated from specific components of the neuropsychological tests, as it has already been done in the past (Desjardins-Crépeau et al., 2014). The composite Z-scores will be computed by averaging the Z-scores of tests and sub-tests assessing the same cognitive functions. The processing speed score includes: DSST score, time to complete SCWIT naming and reading conditions, and time to complete TMT part A. The executive score includes time to complete inhibition and switching conditions of the SCWIT, and time to complete part B of the TMT. The memory score includes the following components from the RAVLT: total number of words recalled in 5 trials, immediate recall after interference, delayed recall, recognition, and false recognitions. Their internal consistency will then be verified using Cronbach’s alpha (Ferketich, 1990).

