### 2.6 Sample size

A power and sample size analysis was performed by a biostatistician team independent of the study team, based on a previous meta-analysis comparing exercise training alone to combined physical and cognitive intervention on cognition (Zhu et al., 2016). Using an intent-to-treat principle with multiple imputations, a sample size of 42 subjects in each group will have 80% power to detect a group difference in means of −0.186 (the difference between a physical alone training mean of 0.239 and a combined training mean of 0.425, for an effect size of 0.624) assuming that the common standard deviation is 0.298 using a two group *t*-test with a 0.050 two-sided significance level. Taking into account a 20% attrition rate observed in our previous exercise studies, we will thus recruit 53 participants per intervention arm (53 × 3 arms), for a total of 159 participants. For the secondary outcome (neuroimaging), we based our calculation on the 2% increase in hippocampal volume following a 12-month physical exercise training reported by Erickson et al. (2011) (Erickson et al., 2011). Results suggest that 60 participants are needed to observe significant changes post-exercise. Since 2 arms involve exercise training in this study (total 106 participants), the numbers of participants are largely enough.

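### The planning SD of 0.298 is not tied to any of the four primary outcomes and fits none of them without strong unstated assumptions, so the 80% power is not shown for them.

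*Protocol article*

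**What the plan says.** Section 2.6 takes its planning figures from a meta-analysis on cognition. The planned contrast is 0.186, which is 0.425 for combined training less 0.239 for exercise alone. The SD enters as an assumption: "assuming that the common standard deviation is 0.298". Dividing the one by the other gives the standardised effect of 0.624. From this the section concludes that "a sample size of 42 subjects in each group will have 80% power". The test behind that statement is run "with a 0.050 two-sided significance level". The section does not say what scale 0.298 is on, whether it describes levels or changes, or which outcome it belongs to.

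Section 2.4.1 defines the outcomes. Global cognition is a raw score: "the Montreal Cognitive Assessment (MoCA) score will measure global cognition". The other three are composites: "The composite Z-scores will be computed by averaging the Z-scores of tests and sub-tests assessing the same cognitive functions". The executive composite has 3 components, processing speed 4 and memory 5, and their internal consistency is to be checked with Cronbach's alpha. Section 2.12 makes change in these four measures the primary outcome, analysed with mixed models adjusted for age, sex and education. The article gives no SD and no baseline-to-follow-up correlation for any of them.

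**The concern.** An SD of 0.298 is small for an average of a few Z-scores, and very small for MoCA in points. Section 2.6 obtains its effect size of 0.624 by dividing by this SD. If the SD does not belong to the outcomes, neither does the effect size nor the power.

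What is at stake is how the result will be read. The primary hypothesis includes multidomain training against exercise alone, two arms that share the same exercise programme. If the real power for 0.186 is well below 80%, a null result could be taken as evidence that cognitive training adds nothing, when the trial could not reliably have detected the difference it was planned around.

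**Working it through.** **1. The plan's own figure.** Inputs from 2.6: means 0.239 and 0.425, SD 0.298, two-sided 0.05, 80% power.
- d = (0.425 − 0.239)/0.298 = 0.186/0.298 = 0.624.
- A two-sample t-test (noncentral t) needs 41.3, so 42 per arm. Power at 42 is 80.7%.
- "Taking into account a 20% attrition rate observed in our previous exercise studies": 42/0.80 = 52.5, so 53 per arm, and 3 × 53 = 159.

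All stated figures reproduce.

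**2. SD of composite levels.** Assume component SDs of 1 and average inter-test correlation ρ. The mean of k components has SD = √[(1 + (k − 1)ρ)/k].

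| Composite | k | SD at ρ = 0 | SD at ρ = 0.3 | SD at ρ = 0.6 | ρ needed for 0.298 |
|---|---|---|---|---|---|
| Executive | 3 | 0.577 | 0.730 | 0.856 | −0.37 |
| Speed | 4 | 0.500 | 0.689 | 0.837 | −0.21 |
| Memory | 5 | 0.447 | 0.663 | 0.825 | −0.14 |

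The last column is (k × 0.298² − 1)/(k − 1). Negative average correlations do not fit composites built from tests of one function and checked for internal consistency. So 0.298 is not the SD of these levels.

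**3. SD of change, or baseline-adjusted.** Let S be the level SD and r the 0–12 month correlation.
- Change SD = S√[2(1 − r)], so r = 1 − 0.298²/(2S²).
- Baseline-adjusted SD = S√(1 − r²), so r = √[1 − (0.298/S)²].

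| Composite | r for change SD 0.298, ρ = 0.3 to 0.6 | r for adjusted SD 0.298, ρ = 0.3 to 0.6 |
|---|---|---|
| Executive | 0.917 to 0.939 | 0.913 to 0.937 |
| Speed | 0.907 to 0.937 | 0.902 to 0.934 |
| Memory | 0.899 to 0.935 | 0.893 to 0.932 |

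The required r is therefore about 0.89–0.94. At ρ = 0 it would be lower: 0.78–0.87 for change and 0.75–0.86 adjusted.

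**4. MoCA.** Assume whole-point scoring.
- Levels: with two adjacent values, p(1 − p) = 0.298² = 0.0888 gives p = 0.099, so about 90% of participants would share one score.
- Change: with changes of −1, 0 or +1 and mean zero, the share that changes is 0.0888, so about 91% would show no change.
- With an assumed level SD of 2 to 3 points, r would have to be about 0.989 (2 points) to 0.995 (3 points) by either formula in step 3.

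**5. Power for 0.186 with 42 per arm, two-sided 0.05.** The article gives no SD, so a range is shown. The last three rows are baseline-adjusted SDs from an assumed level SD of 0.8: 0.8√(1 − r²) at r = 0.9, 0.8 and 0.6.

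| SD analysed | d = 0.186/SD | Power |
|---|---|---|
| 0.298 (stated) | 0.624 | 81% |
| 0.35 (r = 0.9) | 0.531 | 67% |
| 0.48 (r = 0.8) | 0.388 | 42% |
| 0.64 (r = 0.6) | 0.291 | 26% |

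The difference detectable with 80% power at 42 per arm is 0.619 × SD: 0.217, 0.297 and 0.396 for the last three rows.

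**The case against.** **The primary outcome is change, so the level floors do not bind.** This stands. On the change scale 0.298 is demanding but can be reached. For memory with ρ = 0.3 and r = 0.9, the change SD is 0.663 × √0.2 = 0.297. A reader might infer from step 2 that 0.298 is impossible for the composites. The documents do not support that. What they lack is any statement or support for a correlation that high.

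**Component SDs of 1 are an assumption.** This also stands. Section 2.4.1 does not name the reference sample for the Z-scores, and with external norms the component SDs could differ from 1. Adjustment for age, sex and education may also reduce the residual SD somewhat.

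**An effect size of 0.624 has no units and could be assumed for each outcome directly.** It could, but 2.6 derives it from 0.298 instead of arguing for it. With level SDs of 0.66–0.86 it would mean 0.41–0.53 Z units, more than twice the 0.186 stated, and would need its own justification. The same applies to MoCA: 2.6 does not say that 0.186 is in points, so a reader should not conclude that the trial was planned around 0.186 of a point.

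**The derivation may be in a fuller report.** An independent biostatistics team did the calculation and the article is condensed, so the scale of 0.298 may be recorded elsewhere. But the SD, effect and power are printed here as the justification for 159 participants, and they do not match the outcomes printed beside them.

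Two further inferences should be resisted. One is that the meta-analytic means were already standardised and then divided by an SD again. The source is not at hand, so this cannot be established. The other is to add in the Bonferroni threshold of 0.0125, which is a separate question about multiplicity.

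**Conclusion.** The point holds as a mismatch between a planning input and the defined outcomes. It is not an arithmetic error, although a reader might take it for one; step 1 shows the calculation is right for its inputs.

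Given unit-SD components and non-negative correlations, 0.298 is not the level SD of any composite. As an SD of change or a baseline-adjusted residual it depends on a 12-month correlation of about 0.89–0.94 at moderate inter-test correlation. For MoCA in whole points it is not tenable on either scale. The 80% power for a difference of 0.186 is therefore not shown for any of the four primary outcomes.

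Over the assumed SD range of 0.35 to 0.64, power runs from 67% down to 26%. The size of the shortfall depends on SDs and correlations that the article does not give. That the power is unsupported does not depend on them.

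**What to change.** In 2.6, state what 0.298 measures: a between-person SD, an SD of change or something else, and for which outcome. Then replace it for planning with the blinded pooled baseline SD of each of the four outcomes, combined with a stated range of 0–12 month correlations. Restate the power, or the detectable difference, for 42 analysed per arm separately for MoCA in points and for each composite in Z units. Do not keep 0.624 as the planning effect unless it is justified for each outcome.

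The cost is a blinded SD calculation on baseline data and a rewritten paragraph. The drawback is a less favourable power statement. No participants are added, and allocation and treatment code stay concealed.

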### 1.2 Objectives

The goal of this trial is to document the impact of a combined physical and cognitive training intervention on neurocognitive functioning in participants with cardiovascular risk factors, while considering individual factors such as sex and specific alleles and mutations in targeted genes thought to modulate the impact of exercise on cognition and brain functions.

The primary hypothesis will test if the multidomain intervention will show higher cognitive benefits (on global cognition, speed of processing, executive functions, and memory) than the physical exercise training or active control after 12 months of treatment. Secondary objectives will assess if the multidomain intervention will show greater brain imaging benefits (on cerebral autoregulation, cerebral vasoreactivity, cerebral pulsatility, and brain structure) relative to the other two groups. Exploratory objectives will assess if the training improvements are modulated by baseline individual difference factors (like genetic profile, biomarkers, vascular health markers, and psychological markers), but also investigate the potential mediating effects of certain variables that can change over the course of the intervention (e.g., vascular health markers, and psychological markers).

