The primary outcome will be the changes in cognitive performance (MoCA, processing speed, executive functions, and memory). Computerized cognitive tasks will be analyzed separately. We will perform four linear mixed-effects models analyses (for every cognitive measure) with intervention group as fixed factors and adjustments for relevant covariates. An unstructured covariance structure will be used to model the within-patient errors. The final selection of covariates will include age, sex, and education and any potential relevant demographic variable that show a group difference. These will consider, but not be limited to BMI, stress, mood, genetic risk, medical history, and CVRF. A Bonferroni correction will control for multiple comparisons with a significance level set at *p* < 0.0125. The same statistical model will apply for the brain imaging secondary outcomes: pulsatility, vasoreactivity and autoregulation indices, regional cerebral blood flow, grey matter volume and CSVD lesions (Bonferroni-corrected for number of regions). To inform potential future studies, exploratory analyses will also performed in which we will test if certain variable impact the effectiveness of the intervention on the primary (cognition) or secondary (imaging) variables. Due to the exploratory nature of those analyses, no multiple comparison correction will be made and no *a priori* power analysis is made. The exploratory analyses can include but not be limited to testing the mediating or moderating role of the available medical (including cardiovascular health, cardiovascular risk factors), psychological, and biological markers on the group effect. The mediating and moderating analyses will be performed according to the guidelines published by Hayes (2017).

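### The claim that the sample is ample for neuroimaging rests on a pre-post change in two pooled exercise arms, so it does not support the between-arm secondary objective

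*Protocol article*

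**What the plan says.** Protocol article, section 2.6 (Sample size), starts the neuroimaging justification from a published result: "we based our calculation on the 2% increase in hippocampal volume following a 12-month physical exercise training". It continues: "Results suggest that 60 participants are needed to observe significant changes post-exercise". It then concludes: "Since 2 arms involve exercise training in this study (total 106 participants), the numbers of participants are largely enough".

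Section 1.2 (Objectives) states the imaging question: "Secondary objectives will assess if the multidomain intervention will show greater brain imaging benefits". The comparison is made "relative to the other two groups", that is, with physical exercise alone and with active control. The domains listed there are autoregulation, vasoreactivity, pulsatility and brain structure.

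Section 2.12 (Statistical methods) carries the primary model, which has intervention group as a fixed factor, over to imaging: "The same statistical model will apply for the brain imaging secondary outcomes". The imaging tests are "Bonferroni-corrected for number of regions"; the number of regions is not given.

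Section 2.3.2 makes the physical programme of the multidomain arm the same as that of the physical exercise arm, with cognitive training added.

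**The concern.** The 60 and the 106 both refer to change over time in people who exercise. The secondary objective refers to differences between randomised arms. In the multidomain versus exercise comparison the two pooled arms stand on opposite sides. In the multidomain versus control comparison one side is missing from the count altogether. Because both exercise arms follow the same physical programme, a change caused by exercise is common to them and is not the difference between them.

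This is more than a detail left to an analysis plan: the article makes a positive statement of adequacy. The Discussion (section 3) presents the imaging as the way to document how the intervention works. A published assurance that numbers are ample could lead a null multidomain versus exercise result to be read as absence of a mechanism, when the trial may only be able to detect a medium-to-large difference.

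**Working it through.** **1. The plan's own figures (section 2.6).** Inputs for the primary outcome: difference 0.186, SD 0.298, 80% power, a two-group t-test "with a 0.050 two-sided significance level", 20% attrition.
- Effect size: 0.186 / 0.298 = 0.624.
- The exact two-sample t-test needs 41.3 per group, so 42; power with 42 is 80.7%.
- Attrition: 42 / (1 − 0.20) = 52.5, so 53; 3 × 53 = 159; 2 × 53 = 106.

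All of these reproduce. The 60 cannot be reproduced: no standard deviation, pre-post correlation, alpha or power is given for it.

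**2. Which question each number answers.**

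| | Section 2.6 (imaging) | Sections 1.2 and 2.12 |
|---|---|---|
| Quantity | change after exercise | difference between arms |
| Multidomain and exercise arms | added together | compared with each other |
| Active control | not counted | second comparator |
| Endpoint | hippocampal volume | four domains, brain structure among them |
| Multiplicity | not mentioned | Bonferroni by region |

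The mismatch is visible here and needs no assumption.

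**3. Does 106 suffice on its own terms?** ASSUMPTION: the 60 is a paired t-test at two-sided 0.05 with 80% power. The approximate formula is dz = (1.960 + 0.842) / √60 = 0.36; the exact t solution is 0.37. After attrition 106 × 0.8 = 84.8 remain; with 84 the paired power is 91%. For a pooled pre-post change the number is therefore ample, and attrition does not overturn it.

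**4. Scale for the between-arm question.** ASSUMPTIONS: the 20% attrition also holds for imaging, so 53 × 0.8 = 42.4, about 42 per arm; two-sample t-test, 80% power. The approximate formula is d = (z for alpha + 0.842) × √(2/42).
- Two-sided 0.05: (1.960 + 0.842) × 0.218 = 0.61; exact t solution **0.62**.
- Assumed 4 regions, 0.05 / 4 = 0.0125: (2.498 + 0.842) × 0.218 = 0.73; exact **0.74**.
- Assumed 10 regions, 0.05 / 10 = 0.005: (2.807 + 0.842) × 0.218 = 0.80; exact **0.82**.

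**5. Illustrative power with 42 per arm, two-sided 0.05, before correction for regions.** These figures depend on how the 60 is read and on a guessed between-arm difference.

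| Reading of the 60 (80% power) | Contrast | Assumed d | Power |
|---|---|---|---|
| Paired, dz = 0.37 | multidomain vs exercise, whole change | 0.37 | 38% |
| Paired, dz = 0.37 | multidomain vs exercise, half the change | 0.18 | 13% |
| 30 vs 30, d = 0.74 | multidomain vs control | 0.74 | 91% |
| 30 vs 30, d = 0.74 | multidomain vs exercise, half the effect | 0.37 | 38% |

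The range from 13% to 91% shows that the text does not determine the power of the imaging comparison.

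**The case against.** Much of the case for leaving the sentence alone is sound.

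- **The trial is also interested in exercise effects.** The abstract's Discussion and section 1.1 speak of exercise training effects on cognition and brain imaging, and the physical programme is the same in both arms. Pooling them for an exercise effect matches a stated interest. This stands, and it is why the sentence could be kept if limited to that use. It does not extend to the multidomain superiority objective of section 1.2.
- **Hippocampal volume is not off-target.** Brain structure is a named secondary domain, and sizing on one representative endpoint is common. This stands.
- **Attrition is harmless here.** About 85 of 106 would remain, well above 60. This stands.
- **One contrast may be well powered.** Under the 30 versus 30 reading, multidomain versus control has 91% power. This stands.
- **The sentence sets nothing.** Recruitment follows from the primary outcome, and the 0.62 detectable with 42 per arm is about the effect of 0.624 for which the primary is sized. This stands and limits the severity.

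A reader might go further and infer that the imaging comparison is shown to be underpowered, or that section 2.6 contains a calculation error. The document supports neither. It gives no between-arm imaging effect or SD, so the 38% and 13% rest on an assumed test behind the 60 and on an arbitrary share of the exercise change. Every figure in the section that can be recomputed is right.

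**Conclusion.** The adequacy claim is unsupported for the secondary imaging objective. It compares a pre-post requirement with a pooled count that merges the multidomain arm with one comparator and excludes the other. This follows from sections 1.2, 2.3.2, 2.6 and 2.12 alone.

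The useful measure of size is the detectable between-arm difference: about 0.62 SD with 42 per arm, or 0.74 to 0.82 if corrected for an assumed 4 to 10 regions. It assumes that the 20% attrition applies to imaging, a plain two-sample t-test and 80% power. The planned covariate adjustment may improve on it. Completion may also differ by endpoint, since section 2.4.2.1 excludes participants with marked discomfort from the hypercapnia sequence.

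This is a correction to the wording of a power justification for a secondary outcome. It does not affect the primary outcome or the sample size, and it need not hold up the trial.

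**What to change.** In section 2.6, delete the sentence that sets 106 against 60, or limit it explicitly to the pooled pre-post change in hippocampal volume across the two exercise arms. Then add text along these lines:

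*The secondary imaging objective compares the multidomain arm with each of the other two arms. If the 20% attrition assumed for the trial also applies to imaging, about 42 participants per arm will have 12-month data. A two-sample t-test would then have 80% power for a standardised between-arm difference of about 0.62 at two-sided 0.05, before Bonferroni correction for regions (for example 0.74 with 4 regions and 0.82 with 10) and before any gain from covariate adjustment. Completion may differ by imaging endpoint. Imaging differences will be reported with confidence intervals, and a non-significant result will not be taken as evidence that a mechanism is absent.*

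The 4 and 10 regions are illustrations; replace them with the planned number once it is fixed. The cost is a change of wording in the protocol and the matching text of the analysis plan, and the withdrawal or narrowing of a favourable claim. No further scans, participants or design changes are needed.

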### 2.7 Recruitment

Participants are recruited by advertising the study to new members of the EPIC Center, reaching out to community-dwelling adults through online and printed communications (e.g., posters, videos, interviews, newsletters), phone calls to individuals who have agreed to be contacted for a research project, and by the Montreal Heart Institute’s physicians. Interested individuals’ contact information is registered in a password-protected encrypted file with restricted access.

### 2.8 Allocation

#### 2.8.1 Sequence generation

The randomization is stratified by sex (i.e., male/female) to ensure an appropriate balance of the participants’ characteristics between each training arm. The MHICC generated the randomization sequence using computer-generated random numbers sequence using permuted blocks of different undisclosed sizes.

